### Sample size

*Primary and secondary outcome analyses.* Typical effect sizes from randomized controlled trials of MBIs with passive control groups range from ds = 0.10–0.89, with trials in healthcare populations achieving an average effect size of 0.39 and digitally delivered interventions achieving an average effect size of 0.54 [124]. Recruitment capacity for the current trial was 90 participants, given financial and time constraints. Accordingly, we report the minimum detectable effect with 80% power for the primary outcome, perceived stress at the post-intervention assessment, comparing the mindfulness condition with the waitlist control (WLC). The minimum detectable effect was estimated using G*Power [125] for the primary analysis of covariance (ANCOVA; fixed effects, a two-level between-subjects factor, and one covariate), with the baseline value of the outcome entered as the covariate, α = 0.05, power = 0.80, and one numerator degree of freedom. Assuming a baseline–post correlation for PSS of r = 0.50 and the anticipated enrolled sample of 90 participants (45 per condition), of whom approximately 72 are expected to provide complete outcome data after accounting for ~19% attrition, based on a meta-analysis of overall and differential attrition across 114 randomized MBI trials in clinical and non-clinical populations [126], the study provides 80% power to detect a between-group effect of d = 0.58 (Cohen’s f = 0.34). This effect is comparable to the average effect of digitally delivered MBIs relative to passive control conditions (d = 0.54) [124], indicating that the trial is powered to detect effects of the magnitude typically observed for remotely delivered MBIs. In sensitivity analyses varying the baseline–post correlation from r = 0.40 to 0.60, the minimum detectable effect ranged from d = 0.53 to 0.61. The trial is powered for the primary comparison on perceived stress at the post-intervention endpoint. Analyses of secondary outcomes (burnout, depressive symptoms, inflammatory biomarkers, psychological well-being, and sleep quality) will provide estimates of intervention effect sizes but are not powered for definitive hypothesis testing.

*Power for exploratory mediation analyses*. Power for the exploratory parallel mediation model was estimated via Monte Carlo simulation using the application of Schoemann, Boulton, and Short [127]. The model specified group assignment (BEST vs. WLC) as the predictor; compassion, positive emotions, and equanimity/mindfulness at T2 as parallel mediators; and perceived stress (PSS) at T3 as the outcome, with baseline (T1) values of the outcome and each mediator included as covariates. Each specific indirect effect was estimated as the product of its *a* (group→mediator) and *b* (mediator→outcome) paths and tested using a Monte Carlo confidence interval. Intervention-to-mediator effects were derived from meta-analytic estimates comparing mindfulness-based programs with passive control conditions (Hedges’ g = 0.36, 0.44, and 0.22 for compassion, positive emotions, and mindfulness, respectively [75,124,128,129]). Since these are standardized mean differences for a two-group contrast, they were converted to point-biserial correlations for entry into the model (r = g/√(g² + 4), yielding 0.18, 0.22, and 0.11). Mediator–outcome correlations were drawn from prior longitudinal work (r = −0.40, −0.47, and −0.65, respectively [130–132]); the group–outcome correlation was set to −0.24 (corresponding to the anticipated *d* = 0.50 on the primary outcome), and inter-mediator correlations were set to 0.40 (range examined: 0.35–0.45). Based on the anticipated analyzable sample (N = 72; 90 enrolled, ~ 19% attrition), estimated power for each specific indirect effect was low (all < 0.30). Consistent with their preregistered designation, these mediation analyses are therefore exploratory and hypothesis-generating, and the resulting estimates are intended to inform effect-size assumptions for future, adequately powered mediation studies.

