As a complementary, pre-specified sensitivity analysis under a missing-at-random assumption, a linear mixed model will be fit using all available data from all randomized participants with at least one post-baseline observation, with fixed effects for condition and time (categorical) and a random intercept for participants. The between-condition contrast at the post-intervention endpoint will be extracted from this model to correspond to the primary estimand, and change over time and the condition-by-time interaction will be examined as secondary, descriptive analyses [136,137]. As an additional sensitivity analysis, we will repeat the primary outcome models using a per-protocol approach, restricting to participants in the BEST condition who attended at least three of the six intervention sessions (and the corresponding WLC participants), to assess whether the intervention effect differs among those who received the intervention as intended. Since a per-protocol analysis does not preserve the original randomization, it will be interpreted as a complementary, exploratory analysis rather than a confirmatory test of the ITT result. Lastly, because the analyzable sample is modest, the trial is not powered for formal moderation or subgroup analyses. Any examination of whether intervention effects differ across physician subgroups (e.g., specialty) will be exploratory and hypothesis-generating, intended to inform future adequately powered trials rather than to provide confirmatory tests. All tests, primary and secondary outcomes, will be two-sided with an alpha level of 0.05. All analyses will be conducted in R version 4.4.3 [71].

*Mediation analyses.* Mediation analyses will be conducted using the PROCESS macro in R [138]. To enhance the temporal precedence of the intervention’s effect on perceived stress through each mediator, we will assess the outcome (perceived stress) and mediators (compassion, positive emotions, equanimity/mindfulness) for all participants at the midpoint of the six-week intervention (T2). We will fit a parallel mediation model that includes group assignment (BEST vs. WLC) at T1 as the predictor variable, compassion, positive emotions, and equanimity/mindfulness at T2 as the mediators, and PSS scores at T3 as the outcome. The model will control for T1 perceived stress and for each mediator’s T1 values.

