Additionally, the trial’s sample size is also constrained by recruitment capacity, with an anticipated enrolled sample of 90 and projected attrition of approximately 19% [126]. The study is powered to detect a moderate between-group effect (*d* = 0.58), consistent with those typically observed for digitally delivered mindfulness-based interventions [124], but may not detect smaller true effects. Findings should therefore be interpreted as informative about moderate-magnitude effects rather than as definitive tests of smaller ones.

More broadly, our intervention targets individual-level psychological processes, whereas the literature on physician well-being consistently identifies organizational and structural factors—including workload, administrative and clerical burden, electronic health record demands, and scheduling—as major drivers of stress and burnout. BEST is not designed to modify these systemic factors, and our findings should be interpreted accordingly. Should the intervention demonstrate benefits, these effects should be understood as individual-level coping resources that complement, rather than substitute for, organizational efforts to improve provider well-being, and should not be taken to imply that responsibility for addressing burnout rests solely with physicians. Conversely, limited or null effects may reflect constraints imposed by an individual-level approach on organizationally generated stressors rather than the ineffectiveness of the practices themselves. We view individual- and organizational-level approaches as complementary and necessary components of a comprehensive strategy for physician well-being.

Finally, the optional post-intervention feedback form is completed only by intervention-arm participants who choose to respond. These data may therefore reflect self-selection and may not be representative of all participants. We treat these qualitative responses as exploratory rather than as a representative account of intervention acceptability.

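### The minimum detectable effect of d = 0.58 is correctly derived, but it does not support the statement that the trial is powered for effects typical of remote MBIs: complete-case power is about 74% at the 0.54 benchmark

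*Protocol article*

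**What the plan says.** All references are to the protocol article.

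**Sample size, paragraph on primary and secondary outcomes.** The number enrolled, 90, was set by recruitment capacity, so the section reports a minimum detectable effect (MDE) and does not solve for N. With about 72 complete cases and r = 0.50, it gives d = 0.58 (f = 0.34) at 80% power, and a range of 0.53 to 0.61 for r from 0.60 to 0.40. It cites a spread of 0.10 to 0.89 for MBIs against passive controls and two averages: "trials in healthcare populations achieving an average effect size of 0.39", and 0.54 for digital delivery. It calls 0.58 comparable to 0.54, "indicating that the trial is powered to detect effects of the magnitude typically observed for remotely delivered MBIs". It then adds, with no effect size attached, that the primary PSS comparison is adequately powered.

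**Sample size, paragraph on mediation.** The group–outcome correlation is set to −0.24, "corresponding to the anticipated *d* = 0.50 on the primary outcome".

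**Discussion, limitation on sample size.** The detectable effect of 0.58 is described as "consistent with those typically observed for digitally delivered mindfulness-based interventions". The same paragraph warns that true effects below that size could be missed and that the findings are not definitive about them.

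**The concern.** An MDE is a floor. The stated power applies at that effect or above it, and power falls below 80% for anything smaller. The benchmark of 0.54 is smaller than 0.58, so an MDE of 0.58 cannot show 80% power at 0.54. The gap widens for two other figures in the same section: the 0.50 that the mediation paragraph anticipates for this very outcome, and the 0.39 average for healthcare populations, to which physicians belong. Only the largest of the three is carried into the power conclusion.

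PSS is the single confirmatory outcome. A reader who takes the power statement at face value could treat a non-significant result as evidence against an effect of typical size. On the article's own assumptions, the trial would miss a true effect of 0.50 about one time in three, and a true effect of 0.39 slightly more than half the time.

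**Working it through.** **Inputs**
- "α = 0.05, power = 0.80, and one numerator degree of freedom" (Sample size); "All tests, primary and secondary outcomes, will be two-sided with an alpha level of 0.05" (Data analysis plan).
- ANCOVA with "fixed effects, a two-level between-subjects factor, and one covariate" (Sample size).
- "Assuming a baseline–post correlation for PSS of r = 0.50", varied from 0.40 to 0.60 (Sample size).
- N = 72 analysed, equal arms (Sample size). The stated 19% attrition gives 90 × 0.81 = 72.9; using 73 moves each power figure at the three effects below by less than one point.

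**Formula.** Noncentral F with df1 = 1, df2 = 72 − 3 = 69, noncentrality λ = N(d/2)² / (1 − r²), and f = d / (2√(1 − r²)).

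**Step 1: reproduce the article's figure.** At r = 0.50, 1 − r² = 0.75. For d = 0.58, λ = 72 × 0.0841 / 0.75 = 8.07, and power is 80.0%. f = 0.29 / 0.866 = 0.335, against 0.34 stated. The MDE is 0.614 at r = 0.40 and 0.536 at r = 0.60, against 0.61 and 0.53 stated. These agree to rounding (N = 73 gives 0.532 at r = 0.60).

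**Step 2: power at the effects that the article cites or anticipates.** λ at r = 0.50:
- d = 0.54: 72 × 0.0729 / 0.75 = 7.00
- d = 0.50: 72 × 0.0625 / 0.75 = 6.00
- d = 0.39: 72 × 0.0380 / 0.75 = 3.65

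| d | Origin in the article | r = 0.40 | r = 0.50 | r = 0.60 |
|---|---|---|---|---|
| 0.58 | stated MDE | 75.4% | 80.0% | 85.8% |
| 0.54 | average, digital delivery | 69.3% | 74.2% | 80.6% |
| 0.50 | anticipated for PSS, mediation paragraph | 62.6% | 67.6% | 74.4% |
| 0.39 | average, healthcare populations | 42.9% | 47.0% | 53.2% |

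A normal approximation at r = 0.50 gives 75.4%, 68.8% and 48.0% for the last three rows, so the result does not depend on the method.

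**Step 3: is 0.50 really the article's own PSS effect?** A correlation of 0.24 converts to d = 2 × 0.24 / √(1 − 0.24²) = 0.49, and d = 0.50 converts to 0.50 / √(0.25 + 4) = 0.243. The two agree to rounding, so the mediation paragraph does assume an effect on the primary outcome that is smaller than the MDE.

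**Step 4: how much could imputation help?** The planned analysis imputes missing endpoints for all 90 randomized. If imputation recovered everything, an unattainable ceiling, power at r = 0.50 would be 83.3% at 0.54, 77.3% at 0.50 and 56.1% at 0.39.

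**The case against.** The strongest reply is that this is a small matter of wording around a correct calculation, and much of that reply stands.

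- The sentence at issue concerns remote delivery, for which the article's benchmark is 0.54. The shortfall there is about 6 points at r = 0.50, and the text says comparable, not equal. At r = 0.60, inside the article's own range, power at 0.54 reaches 80.6%. The 0.39 is openly reported, and the 0.50 is an input to an exploratory calculation. This stands: those two figures do not contradict the remote-delivery sentence itself. They do bear on the separate, unqualified statement that the primary comparison is powered.
- The figure of 72 is a complete-case count, whereas the analysis will use multiple imputation with a mid-course PSS available. This also stands: 74% is conditional and is not the trial's true power. Imputation may recover something, but the documents do not say how much.
- The Discussion already cautions about smaller effects. It does, and that limits the harm. But it still calls 0.58 typical, so a reader cannot tell that 0.54, 0.50 and 0.39 all count among the smaller effects.

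Three stronger readings may tempt a reader, and the documents support none of them. The MDE does not exceed every effect cited, because the spread of 0.10 to 0.89 extends above it; it exceeds every average or anticipated value. There is no arithmetic error in the MDE. And the article does not hide its constraint: it says that capacity fixed the sample and gives the MDE, its range and the benchmarks.

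**Conclusion.** The MDE is right and the conclusion drawn from it is wrong as worded. In the base case (72 complete cases, r = 0.50, two-sided 5%), the design has about 74% power at the remote-delivery average of 0.54, 68% at the article's own anticipated 0.50 and 47% at its healthcare average of 0.39. Over r = 0.40 to 0.60 the ranges are 69–81%, 63–74% and 43–53%. With 72 complete cases, only the 0.54 benchmark reaches 80%, and only near the top of that range. The Sample size section also leaves unreconciled the 0.54 used as benchmark for PSS and the 0.50 anticipated for it.

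The figures rest on the article's assumed correlation and attrition, and imputation could raise them somewhat. This should be corrected because it governs what a null PSS result can be said to show. It is not a fault in the design or the planned analysis.

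**What to change.** In the Sample size section and the Discussion:

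1. Replace the claims that the trial is powered for typical effects, and that 0.58 is in line with them, by the MDE (0.58; about 0.53 to 0.61 over r) and the power at 0.54, 0.50 and 0.39. Label these as conditional on r and on 72 complete cases. Attach the MDE to the general statement about the primary comparison.
2. Use one anticipated PSS effect in the primary and mediation paragraphs, or explain why they differ.
3. Extend the Discussion's caveat: non-significance on PSS does not by itself rule out effects of 0.39 to 0.54, and the result will be read from its 95% confidence interval.

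The cost is a few sentences and a less favourable power statement. No participants, procedures or analyses change.

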### Data analysis plan

*Descriptive analyses.* Descriptive statistics will be created to show the demographic and psychological characteristics of the sample. Baseline demographic and occupation-related characteristics will be summarized descriptively by condition (BEST and WLC) using means and standard deviations for continuous variables and frequencies and percentages for categorical variables. In addition to standard demographic characteristics, we will summarize sources of heterogeneity within the physician sample, including medical specialty, workload, and career stage, to characterize the sample’s composition across these dimensions. No inferential tests of baseline differences will be conducted. Consistent with our preregistered analysis plan, the primary outcome models adjust for the baseline value of the outcome, regardless of observed baseline balance. Additionally, we will examine the distributional properties of the study variables to assess normality. We will address issues of non-normality using applicable techniques, including robust standard errors and rescaling. It is common practice to log-transform inflammatory markers to normalize distributions.

*Feasibility and acceptability.* Analyses of feasibility and acceptability will be primarily descriptive and will be evaluated against the pre-specified benchmarks described above. Feasibility will be summarized as the number of participants recruited during the recruitment period, the proportion retained through the post-intervention assessment, and session attendance. Attendance will be reported as the number of sessions attended (including the full distribution across participants) and as the proportion of participants who meet the completion threshold of at least three of six sessions. Acceptability will be summarized using mean Treatment Satisfaction Questionnaire (TSQ) scores, evaluated against the pre-specified acceptability benchmark, together with the dimension-specific ratings from the optional feedback form (overall quality, relevance, clarity of instruction, and pacing/structure), reported separately to characterize distinct components of acceptability. The open-ended feedback form responses will be summarized qualitatively to identify specific features that participants found more or less acceptable. Where sample size permits, feasibility and acceptability will additionally be summarized across relevant subgroups (e.g., specialty) to examine heterogeneity. These subgroup summaries will be descriptive and exploratory.

*Primary and secondary outcomes.* All analyses will employ an intention-to-treat (ITT) principle. Thus, regardless of how many classes they attended or assessments they completed, all randomized participants will be included in analyses and analyzed based on their original group assignment [133]. When possible, we will record the reasons for discontinuing participation, properly annotate them in the CONSORT diagram, and retain the data for potential exploratory subgroup analyses.

All outcome models adjust for a pre-specified set of covariates, determined a priori on substantive grounds rather than on observed baseline balance. For each outcome, the primary ANCOVA includes the baseline (T1) value of that outcome as a covariate. Additionally, analyses for inflammatory markers will control for variables known to influence inflammation (e.g., BMI). In keeping with our preregistered analysis plan and CONSORT guidance, covariates are held fixed across analyses regardless of any observed baseline differences between conditions. All primary and secondary outcomes are continuous and assessed at multiple time points. The primary hypothesis concerns the between-condition difference in each outcome at the post-intervention endpoint. Accordingly, the primary analysis will be an ANCOVA comparing conditions (BEST vs. WLC) for each outcome at the post-intervention endpoint, adjusting for baseline (T1) values. ANCOVA is specified a priori as the primary model based on the study design. Covariates are pre-specified as described above. Perceived stress is the single confirmatory primary outcome and is tested at α = 0.05, requiring no adjustment for multiplicity. The secondary outcomes (burnout, depressive symptoms, psychological well-being, sleep quality, and inflammatory biomarkers) are pre-specified but interpreted as exploratory. These analyses will provide effect-size estimates and are reported without formal confirmatory claims or adjustment for multiple comparisons, informing future adequately powered trials rather than definitively testing efficacy.

We anticipate approximately 19% attrition based on comparable mindfulness-based intervention trials [126], and the extent and reasons for missing outcome data will be reported by condition in the CONSORT flow diagram. Our analyses assume that data are missing at random (MAR) conditional on baseline covariates and observed outcomes, an assumption supported by the collection of baseline and intermediate measures likely to predict missingness. To maintain the ITT principle under this assumption, missing endpoint data will be addressed using multiple imputation [134], with ANCOVA estimates pooled across imputed datasets according to Rubin’s rules [135].

As a complementary, pre-specified sensitivity analysis under a missing-at-random assumption, a linear mixed model will be fit using all available data from all randomized participants with at least one post-baseline observation, with fixed effects for condition and time (categorical) and a random intercept for participants. The between-condition contrast at the post-intervention endpoint will be extracted from this model to correspond to the primary estimand, and change over time and the condition-by-time interaction will be examined as secondary, descriptive analyses [136,137]. As an additional sensitivity analysis, we will repeat the primary outcome models using a per-protocol approach, restricting to participants in the BEST condition who attended at least three of the six intervention sessions (and the corresponding WLC participants), to assess whether the intervention effect differs among those who received the intervention as intended. Since a per-protocol analysis does not preserve the original randomization, it will be interpreted as a complementary, exploratory analysis rather than a confirmatory test of the ITT result. Lastly, because the analyzable sample is modest, the trial is not powered for formal moderation or subgroup analyses. Any examination of whether intervention effects differ across physician subgroups (e.g., specialty) will be exploratory and hypothesis-generating, intended to inform future adequately powered trials rather than to provide confirmatory tests. All tests, primary and secondary outcomes, will be two-sided with an alpha level of 0.05. All analyses will be conducted in R version 4.4.3 [71].

*Mediation analyses.* Mediation analyses will be conducted using the PROCESS macro in R [138]. To enhance the temporal precedence of the intervention’s effect on perceived stress through each mediator, we will assess the outcome (perceived stress) and mediators (compassion, positive emotions, equanimity/mindfulness) for all participants at the midpoint of the six-week intervention (T2). We will fit a parallel mediation model that includes group assignment (BEST vs. WLC) at T1 as the predictor variable, compassion, positive emotions, and equanimity/mindfulness at T2 as the mediators, and PSS scores at T3 as the outcome. The model will control for T1 perceived stress and for each mediator’s T1 values.

Based on recommendations by MacKinnon et al. [139], we will test the significance of the indirect effects using a non-parametric bootstrap approach (5,000 samples), which yields an average point estimate and a 95% confidence interval (CI) for the indirect, direct, and total effects. The effect is considered significant if the CI does not include zero [138].

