**Fig 2 pone.0357906.g002:**
[figure not shown]
Participant Flow Diagram.

Using a 1:1 allocation, we will randomize 90 participants to the BEST intervention (n = 45) or WLC (n = 45). Primary, secondary, and exploratory outcomes will be assessed at baseline, mid-course, and post-intervention (after week 6 of the six-week intervention).

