### Procedures and study flow

*Eligibility Screening, Informed Consent, and Baseline Assessment (T1).* Interested individuals will contact the study team via email or phone. The principal investigator will then call potential participants to confirm eligibility criteria. Participants will be recruited in cohorts of 20–30 physicians, who will be randomly assigned to either the BEST group or the WLC, allowing for our desired mindfulness group size of 10–15 participants. Screening will continue until we have an adequate number of eligible, interested, and available participants for the next cohort.

All eligible participants will then review and verbally acknowledge the IRB-approved consent form. After obtaining consent and enrollment, participants will be automatically emailed a link to complete the study questionnaires through Qualtrics. They will also receive an at-home blood collection kit in the mail to provide a blood sample for immune evaluation. Participants will be advised to complete the blood collection in the morning to control for diurnal variations in immune parameters. Based on pilot completion data, the questionnaire battery takes approximately 20–30 minutes, and blood specimen collection requires approximately 10 minutes. Baseline assessments will be conducted during the 2 weeks preceding the first class of the intervention. The principal investigator conducts eligibility screening and consent, and the distribution of assessment links is automated through Qualtrics.

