During each session, participants receive structured training and instruction in meditation exercises, including theoretical background, formal guidance on the day’s topic, and question-and-answer sessions to support learning. Additionally, participants will be guided through each meditation exercise introduced during class. Furthermore, each class will include dyadic discussions, allowing participants to interact directly with one another. The sessions will introduce the following topics and associated practices: 1) introduction to mindfulness, 2) mindfulness and self-compassion, 3) self-directed kindness, 4) compassion, 5) equanimity, and 6) joy. The BEST intervention also includes home practice, in which participants are encouraged to practice the meditation technique introduced in class at home, starting with five minutes and gradually increasing to 20 minutes per day throughout the six weeks of the intervention. All sessions will be delivered by the intervention developer, who has nearly 30 years of experience teaching meditation.

*Waitlist Control (WLC).* The WLC will control for naturally occurring changes in the outcomes and mediators over the assessment period. Participants in this group will not engage in any study-related activities outside of the remote assessments (baseline, mid-course, and post-intervention). Participants randomized to this condition will be offered the BEST intervention after all data collection is completed.

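### BEST is taught in about 3–4 interactive groups, but the primary ANCOVA, the mixed model and the detectable effect of d = 0.58 assume independent participants

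*Protocol article*

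**What the plan says.** **Delivery.** Under Procedures and study flow, physicians enter in cohorts of 20–30 and are randomised to BEST or waitlist, "allowing for our desired mindfulness group size of 10–15 participants". Under Intervention conditions, BEST consists of six weekly one-hour Zoom group sessions, and "each class will include dyadic discussions, allowing participants to interact directly with one another". One instructor, the developer, teaches every session. Waitlist participants only complete assessments.

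**Analysis.** Under Data analysis plan, "For each outcome, the primary ANCOVA includes the baseline (T1) value of that outcome as a covariate". Further covariates, such as BMI, are added only for inflammatory markers, and covariates are held fixed across analyses. The sensitivity mixed model has condition and time as fixed effects and a random intercept for participants. Robust standard errors are offered only as a response to non-normality. Perceived stress is the single confirmatory outcome, and "All tests, primary and secondary outcomes, will be two-sided with an alpha level of 0.05".

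**Sample size.** The MDE comes from a G*Power ANCOVA ("fixed effects, a two-level between-subjects factor, and one covariate") with "α = 0.05, power = 0.80, and one numerator degree of freedom". With about 72 completers and a baseline–post correlation of 0.50, it is d = 0.58 (f = 0.34). No ICC or design effect appears. The Discussion repeats d = 0.58 and does not list clustering among the limitations.

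**The concern.** This is a partially nested design. BEST participants share sessions, discussion partners and a group atmosphere; waitlist participants share nothing of the kind. If BEST outcomes correlate within groups, 36 BEST completers carry less information than 36 independent people. The ANCOVA does not know this. Its standard error for the treatment contrast is then too small, and the MDE is understated for the same reason.

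The test at stake is the only confirmatory one in the trial. The article also uses the MDE to argue that the trial can detect effects of the size usual for digital mindfulness programmes (d = 0.54).

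This is not detail left to a separate document. The article itself fixes the model, its covariates, the random-effect structure and the MDE, and it relies on preregistration to restrain an unblinded analyst.

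**Working it through.** **Inputs from the article.** 45 per arm; about 72 completers, so 36 per arm; r = 0.50; two-sided α = 0.05; power 0.80; BEST groups of 10–15.

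**Assumption.** The ICC is not given. Values of 0.01 to 0.10 are tried, defined on the baseline-adjusted residual.

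**Step 1: number of groups.** 45/15 = 3 and 45/11 ≈ 4. Among 36 completers this means m = 12 per group (k = 3) or m = 9 per group (k = 4).

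**Step 2: the article's own figure.** The noncentral F with 1 and 69 df and λ = 72f² gives f = 0.335 at 80% power. Then d = 2f√(1 − r²) = 2 × 0.335 × √0.75 = 0.58. The stated figure reproduces, and it corresponds to ICC = 0.

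**Step 3: clustering in BEST only.**
- Design effect in BEST: DE = 1 + (m − 1) × ICC.
- SE² = 0.75 × (DE/36 + 1/36).
- Ratio of true to assumed SE: R = √((1 + DE)/2).
- MDE with 69 df = 0.58 × R.
- Actual type I error of the planned test ≈ 2 × P(t₆₉ > 1.995/R).

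Example: ICC = 0.05 and m = 12 give DE = 1 + 11 × 0.05 = 1.55, R = √1.275 = 1.129, and MDE = 0.58 × 1.129 = 0.655.

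| ICC | DE (k = 4 / 3) | R (k = 4 / 3) | MDE, 69 df (k = 4 / 3) | Power at d = 0.58 (k = 4 / 3) | Type I error, formula (k = 4 / 3) |
|---|---|---|---|---|---|
| 0 | 1.00 / 1.00 | 1.000 / 1.000 | 0.58 / 0.58 | 80% / 80% | 5.0% / 5.0% |
| 0.01 | 1.08 / 1.11 | 1.020 / 1.027 | 0.59 / 0.60 | 78% / 78% | 5.4% / 5.6% |
| 0.02 | 1.16 / 1.22 | 1.039 / 1.054 | 0.60 / 0.61 | 77% / 76% | 5.9% / 6.2% |
| 0.05 | 1.40 / 1.55 | 1.095 / 1.129 | 0.64 / 0.66 | 73% / 70% | 7.3% / 8.2% |
| 0.10 | 1.80 / 2.10 | 1.183 / 1.245 | 0.69 / 0.72 | 66% / 61% | 9.6% / 11.4% |

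Repeated simulations of the planned ANCOVA, with a zero mean effect and clustering in BEST only, gave 5.8–6.6% at ICC 0.02, 7.0–8.9% at 0.05 and 9.6–11.7% at 0.10.

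**Step 4: small-sample degrees of freedom.** With k groups, the Satterthwaite approximation is df = (DE + 1)² / (DE²/(k − 1) + 1/35). For ICC = 0.05 and k = 3: 2.55² / (1.55²/2 + 1/35) = 5.3. The MDE (k = 4 / 3) is then 0.66 / 0.72 at ICC 0.02, 0.71 / 0.80 at 0.05 and 0.79 / 0.93 at 0.10. Part of this is only the cost of having few groups: at ICC = 0 the same approach gives 0.63 / 0.66.

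**Step 5: does a cohort factor help?** Simulated type I error (k = 3 / 4, clustering in BEST only, 12,000 runs per setting):

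| ICC | Planned ANCOVA | With fixed cohort factor |
|---|---|---|
| 0.02 | 6.6% / 5.8% | 6.7% / 5.7% |
| 0.05 | 8.5% / 7.1% | 8.6% / 7.1% |
| 0.10 | 11.4% / 9.8% | 11.7% / 10.0% |

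With one BEST group per cohort, a cohort term cannot remove variation that exists only in the BEST arm from the treatment contrast.

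**Step 6: cohort effects shared by both arms.** With shared effects alone (four cohorts, ICC 0.05 and 0.10), the planned ANCOVA rejected in 4.5% and 4.3% of runs, slightly below nominal. With a BEST-group ICC of 0.01 and a shared cohort ICC of 0.05, it rejected in about 4.7–5.3%.

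**The case against.** **The ICC may be small.** One developer teaches every group from a manual, so instructor differences add nothing. Contact is six one-hour Zoom sessions, and participants may come from different healthcare systems. At ICC 0.01–0.02 the MDE is 0.59–0.61, inside the article's own sensitivity range of 0.53–0.61. This stands as an argument about size. It does not show that the ICC is zero, because peer discussion and group dynamics remain.

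**The MDE drives no decision.** Recruitment capacity set the sample size, and the Discussion already warns that smaller effects may be missed. This also stands, but that warning is tied to d = 0.58 and says nothing about grouping.

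**If BEST changed nobody, it could create no group-specific effect.** This is correct. The inflation applies to a null in which groups truly differ but their average effect is zero.

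**Stronger readings that a reader might infer.** One is that any positive group ICC pushes the test above 5%. Step 6 does not support this, since shared cohort effects can offset a small BEST-group ICC. Another is that ignoring cohort or calendar time also makes the error bars too narrow. It works the other way: effects common to both arms largely cancel when the arms are balanced within cohort, and leaving them out is slightly conservative. A third is that adjusting for cohort repairs the test; Step 5 shows that it does not.

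**Conclusion.** The point holds in a limited form. The grouping is fixed by the design, and none of the three calculations allows for it. The figure d = 0.58 is right only if there is no within-group correlation. Confidence in the direction is high, provided that BEST outcomes correlate within groups beyond what both arms share. Confidence in the size is moderate to low, because it rests on an assumed ICC and on three or four equal groups. The effect is negligible at ICC 0.01 and material from about 0.05.

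This should be fixed, but it does not invalidate the trial. A reader might conclude that the confirmatory ANCOVA must be replaced. The documents do not support that: no ICC is given, and with three or four groups the between-group variance is too poorly estimated for a nested model to be more than a sensitivity analysis.

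**What to change.** 1. Before outcome data are accessed, register a partially nested mixed model as a sensitivity analysis for perceived stress. It should have a random group effect in the BEST arm only, waitlist participants as singletons, and Kenward–Roger or Satterthwaite degrees of freedom. Report the group ICC with its uncertainty.
2. In Sample size and in the Discussion, state that d = 0.58 assumes no within-group correlation. Give the MDE over an assumed ICC range, about 0.60–0.66 for ICC 0.02–0.05 with 69 df, and note that it is larger with small-sample df.
3. List BEST-group clustering in the Discussion as a limitation of the confirmatory test.

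Recruitment cohort may be added as a fixed factor for precision, but should not be presented as a correction for clustering.

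The cost is a little analysis work, a slightly less favourable MDE, and a wide confidence interval from the nested model. Data collection runs to December 2026 and outcome data are not to be accessed for analysis before it ends, so the change can still be made in advance.
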